#### 2.2.6. Participant Safety

PCP approval will be required before potentially eligible patients are contacted by the study. Participants will be carefully screened and individuals for whom the interventions would be medically inappropriate or unsafe are excluded. During screening, women who are pregnant, lactating, or planning to become pregnant during the study period are excluded. If a participant becomes pregnant during the study, she is excluded immediately from further participation in all study activities, and her PCP is immediately notified. Participants who develop any other exclusionary condition (e.g., diabetes) following randomization may continue with the interventions and follow-up assessments with their PCP’s approval. To ensure unbiased ascertainment between the intervention and control group, outcome assessors will systematically screen all participants for adverse events during in-person assessments at baseline, 12, and 24 months using a standard interview and reporting form as done in our previous trials. In addition, outcome assessors will call all patients at six and 18 months to screen for adverse events. Positive responses trigger an adverse event record, which is reviewed by the study physician for seriousness, study relatedness, and expectedness. Similar information reported by participants at other times (e.g., during intervention encounters) is duly noted and followed up with, as needed, to assure participant safety. Participants will be referred to their PCP for a medical evaluation and follow-up as needed or recommended by the study physician. We will report adverse events according to the data and safety monitoring plan (**Appendix A**).

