### 2.2.8.1. Primary and secondary outcomes (Aim 1)

Primary outcome, weight, will be assessed according to standard protocols. Secondary outcomes include measures of cardiometabolic risk factors (e.g., BMI, waist circumference, and blood pressure), psychosocial well-being (e.g., health-related quality of life), and behavior change (e.g., diet, physical activity). Trained bilingual research assistants will conduct anthropometric and blood pressure measurements, and multiple-pass 24-hour dietary recalls. Online self-administered questionnaires and in-person interviewer-administered questionnaires (see **Table 2**) will be used to assess additional secondary outcomes including physical activity, health-related quality of life, obesity-specific quality of life, depressive symptoms, and sleep habits and quality. All these surveys have been validated in English and Spanish. Additionally, we will abstract data from the EHR on laboratory values (e.g., HbA1c, fasting glucose, lipid levels), medication prescriptions, and health care encounters for 24 months before and after randomization.

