#### 2.2.9.2. Sample size and data interpretation

We power this trial on change in weight in kg from baseline to 24 months (primary endpoint). To estimate power, we use a *t*-test with simplified assumptions that compares (24m - baseline) differences between study arms at  $\alpha = 5\%$  (2-sided). Actual power may be greater due to increased efficiency associated with repeated-measures mixed models with baseline and covariate adjustments. A sample of 93/arm has 80% power to detect a net between-treatment *M* (SD) difference of 2.1(4.6) kg, assuming up to a 20% loss to 24 months of follow-up. As a conservative estimate, this effect size is based on the net weight change in the E-LITE self-directed intervention (corresponding to a mean of 4.5kg, 5.0% weight loss vs. 2.4kg, 2.6% in usual care), which was significantly smaller than that of the coach-led group (6.3 kg-; 6.6% weight loss). Weight loss  $\geq 5\%$  is widely regarded to be clinically significant, whereas a weight change  $< 3\%$  has been used to define weight maintenance. Hence, the net weight change for the E-LITE self-directed intervention relates to the minimal clinically important difference in weight reduction. To preserve statistical power, no multiplicity adjustment will be made for secondary analyses. These analyses are not intended to produce clinically actionable results, but to supplement conclusions based on the primary analysis, and to inform future research. They will be interpreted properly within that context, considering the totality of evidence available.

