| Implementation success during intervention delivery ( staff perspective )   | Via surveys of lifestyle coach we will assess their perceptions of (1) consistency of intervention procedures, (2) intervention suitability for primary care, and (3) experience with the strategies facilitating intervention delivery (e.g., training, supervision, audit and feedback). We will measure the costs of intervention personnel and supplies. | Via interviews with lifestyle coach, PCPs, and clinic leadership we will ask: What were the barriers to and enablers of delivering the intervention? How might these factors translate (or not) to implementation after the study ends? Were certain components more challenging to deliver than others? What modifications could be made to maximize implementation success? |
| Implementation success during intervention delivery ( patient perspective ) | We will assess intervention participants' engagement and adherence by monitoring the number of group sessions attended, reasons for missed sessions, secure e-messaging and self-monitoring frequency, and adherence across participant subgroups.                                                                                                           | Via interviews with a random sample of participants we will ask: How culturally relevant and acceptable were the knowledge and skills gained? How often did they practice the intervention strategies? What were the perceived benefits? What problems did they encounter? How satisfied were they with program format, materials, and coach performance?                     |
| Maintenance of intervention effects in individuals and settings over time          | Aim 1 focuses on individual-level sustainability of the intervention effects through 24 months. Additionally, we will assess attrition and adverse events by participant characteristics and treatment condition.                                                                                                                                            | Via interviews with lifestyle coach, PCPs, and clinic leadership we will ask: How could the intervention be integrated into regular care and sustained after the study ends? What resources, policies, and care process redesigns would be needed to maximize sustainability?                                                                                                 |

547

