## 548 **Appendix A. Vida Sana Data and Safety Monitoring Plan**

549 The following procedures will be followed to ensure the safety of study participants and the  
550 validity and integrity of data in compliance with NIH requirements.

**Functions of the Data and Safety Monitoring Board (DSMB).** A DSMB in the context of this investigator-initiated randomized controlled trial exists for the purpose of providing the investigators, the cognizant IRB, and the sponsor with objective scientific monitoring of the conduct of the study from the standpoint of ensuring the protection and safety of human subjects and the validity and integrity of the trial. The DSMB will be an independent, advisory body to the investigators and funding agency. To fulfill its functions, the DSMB will review the original protocol and any subsequent amendments, perform expedited monitoring of all serious adverse events (SAEs), perform ongoing monitoring of drop-outs and non-SAEs, determine whether study procedures should be changed or the study should be halted because of serious safety concerns and/or major problems with the study conduct, and perform periodic review of the completeness and validity of data to be used for analysis of safety and efficacy. The DSMB also will monitor implementation of procedures to ensure research participant privacy and data confidentiality.

As in any clinical trial, it is not possible to anticipate all possible adverse events (AEs). We will conduct extensive training with our staff on ascertaining, monitoring, and documenting AEs, serious or not. The study investigators have extensive experience in clinical trials organization and management, including data and safety monitoring for single site and multi-site trials. We have established procedures for rendering first aid in life threatening emergencies.

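### Adverse event detection rests wholly on participant report, with more opportunity in the intervention arm, and the EHR encounters already planned for everyone are not named as a safety source

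*Protocol*

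**What the plan says.** Section 2.2.6 sets out the ways an adverse event comes to light. First, "outcome assessors will systematically screen all participants for adverse events during in-person assessments at baseline, 12, and 24 months". Second, there are telephone screens: "In addition, outcome assessors will call all patients at six and 18 months to screen for adverse events". Third, "Similar information reported by participants at other times (e.g., during intervention encounters) is duly noted and followed up with, as needed". What follows depends on the participant's answer: "Positive responses trigger an adverse event record, which is reviewed by the study physician for seriousness, study relatedness, and expectedness". The section gives unbiased ascertainment between the arms as the reason for systematic screening. It also takes a participant who becomes pregnant out of all study activities.

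Appendix A requires every SAE to be reported to the Data and Safety Monitoring Board (DSMB), whether or not it is related to the study. Its definition covers death, inpatient hospitalisation and congenital anomaly, among others. Table 3 (Maintenance row) adds a by-arm comparison: "we will assess attrition and adverse events by participant characteristics and treatment condition".

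Elsewhere, section 2.2.8.1 plans EHR abstraction of laboratory values, "medication prescriptions, and health care encounters for 24 months before and after randomization". The eligibility table makes authorisation of EHR extraction an entry condition, so it covers every participant. Section 2.2.4 also takes physician orders and referrals from the EHR in both arms, to describe obesity treatment outside the study. Neither section 2.2.6 nor Appendix A names the EHR as a source of adverse events.

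**The concern.** There are two gaps. The first is coverage. If every route depends on the participant, the route fails for those in whom a serious event may be the reason for silence: people who have died, are too ill to respond, or have dropped out. The DSMB is to receive all SAEs, but it can receive only those that are discovered.

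The second is comparability. The protocol's one example of an unscheduled report is an intervention encounter, and controls have none. The same event could be recorded from an intervention participant at the next session and wait for the next six-monthly screen in a control. A difference between arms, or the absence of one, could then reflect opportunity to report rather than safety. That works against the stated aim of unbiased ascertainment and weakens both the by-arm table and the blinded-group summaries sent to the DSMB.

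**Working it through.** **1. The plan's own figure.** The loss rate comes from section 2.2.9.2, which sizes the trial at 93 per arm, "assuming up to a 20% loss to 24 months of follow-up". With a difference of 2.1 kg, SD 4.6 kg, two-sided alpha 0.05 and 80% power, n = 2 × (1.960 + 0.842)² × (4.6/2.1)² = 75.3, so 76 completers per arm; 76/0.80 = 95. With 93 × 0.80 = 74.4 completers per arm, power is 79.5% by the normal approximation. The stated figure reproduces closely and is not in dispute. It is used here only for the 20%.

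**2. Who may miss the last screen.** 0.20 × 186 = 37.2, or about 37 participants (18.6 per arm if loss is equal). This is a ceiling set for the 24-month weight endpoint.

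**3. Follow-up time without safety contact.** Planned follow-up is 186 × 2 = 372 person-years. The protocol does not say when loss occurs, so the unobserved time per lost participant is an assumption:

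| Assumed years without contact, each | Person-years (37.2 × years) | Share of 372 |
|---|---|---|
| 0.5 | 18.6 | 5% |
| 1.0 | 37.2 | 10% |
| 1.5 | 55.8 | 15% |

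No SAE rate is given, so these shares cannot be turned into a number of missed events.

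**4. Opportunity to report, by arm.** Scheduled screens after baseline: 4 in each arm (6, 12, 18 and 24 months). Group sessions (section 2.2.5.2): 12 weekly + 4 bi-weekly + 6 monthly = 22, intervention arm only. Scheduled contacts over 24 months are therefore 4 for a control and 4 + 22 = 26 for an intervention participant, before counting the coach's weekly feedback in the core phase (section 2.2.5.3). In the first 12 months the count is 2 against 24.

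**5. Routes set against requirements.**

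| Event to be reported | Stated way of finding it | EHR data already planned |
|---|---|---|
| Hospitalisation, participant in contact | Screen or volunteered report | Encounters to 24 months |
| Hospitalisation, participant not reachable | None stated | Encounters to 24 months, if recorded in the practice's EHR |
| Death | None stated | Possibly, if recorded there |
| Congenital anomaly after removal for pregnancy | None stated | Possibly, if recorded there |

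**The case against.** The strongest reply is that this is a reasonable design for a behavioural trial in patients cleared by their physicians. The same solicited interview is given to both arms, missed visits are followed by attempts to re-contact (section 2.2.7), and an independent DSMB sees all reported SAEs, retention and reasons for dropout. No passage contradicts another. The EHR belongs to a group practice, and the protocol does not say that inpatient admissions or deaths appear in it. Nor does it say how often abstraction will take place; a single extraction at the end would fit the text. All of this stands, and it limits both the weight of the point and the yield of the remedy. But re-contact and a list of dropout reasons are not SAE detection procedures, and equal screens do not equalise the unscheduled route.

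A reader might infer more than the protocol supports:

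- *Events are found only by asking every six months.* Unscheduled reports are accepted too; six-monthly screening is the only systematic source.
- *The intensive phase passes unobserved because the first screen follows it.* Only intervention participants have that phase, and the coach sees them throughout it.
- *Those lost to follow-up, 37 people, go unobserved.* A person with no 24-month weight may have been screened at 6, 12 and 18 months.
- *Discovery takes three months on average, against a two-day notice.* Three months is an upper bound that assumes nobody reports between screens. The notice runs from discovery and covers unanticipated SAEs, so late discovery does not breach it.
- *Many quarterly DSMB reviews would hold nothing new.* Three sequential cohorts stagger up to 186 × 4 = 744 planned screens over calendar time.

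**Conclusion.** The point holds as a worthwhile and inexpensive improvement to safety ascertainment. It does not touch the primary analysis or the sample size. The text establishes three things: every stated route to an adverse event depends on participant report; the unscheduled route is much more open to the intervention arm (26 scheduled contacts against 4); and EHR encounters that could partly close the gap are planned for all participants but not named for safety use.

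The size is bounded only loosely. At most about 37 of 186 participants miss the 24-month screen if loss reaches the planning ceiling, and 5% to 15% of planned person-years lack safety contact under the assumed 0.5 to 1.5 years each. The direction and size of any bias in by-arm rates are unknown, because the protocol gives neither the timing of loss nor an SAE rate. Easier reporting in the intervention arm could make the intervention look less safe, while loss related to illness could act either way. Sources of SAEs belong in the protocol's safety section and monitoring plan. Both are shown, and neither points to a further safety document.

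**What to change.** In section 2.2.6 and Appendix A, name the EHR health care encounters of section 2.2.8.1 as a second source of SAEs, reviewed by staff masked to arm.

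- Screen them for hospital admissions and deaths in all randomised participants through month 24, including those who no longer attend, unless EHR authorisation has been withdrawn.
- Do this at least at the planned abstraction, and preferably before each quarterly DSMB report.
- Send each hit to the study physician as an adverse event record, on the same footing as a positive interview response.
- Report by-arm SAE rates twice: from the systematic screens alone, where opportunity to report is equal among those interviewed, and from screens plus EHR, which adds participants who were not interviewed. State how many participants contribute to each.
- State in the protocol which admissions and deaths the practice's EHR is expected to capture.

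The cost is a short protocol change and some additional physician review. If the query is quarterly, there is extra abstraction work, since the protocol fixes the abstraction window but not its frequency. Participants carry no added burden. Admissions and deaths outside the practice's EHR may still be missed, and the report should say so.

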#### 2.2.7. Retention

As we have done in our previous trials, we will maximize adherence and retention by careful selection and training of staff, systematic quality control, and adhering to high-quality practices to maintain subject participation in the study. We will use a tracking database to facilitate coordination and monitoring of participant-level activities. No individuals will be randomized without eligibility verification or complete baseline data. Examples of processes that facilitate retention at follow-up include thorough and fully informed roles and responsibilities of staff and participants, conveying an appreciation of participation and study identification, nominal remuneration for study visits, reasonable accommodations to participant schedules, and prudent participant incentives (pedometer and cash incentives). We will contact participants who miss a visit to reschedule and to re-engage them in subsequent follow-ups. Using a combination of these strategies, we have consistently achieved high retention in several RCTs of similar scope, including those with Latino participants.

## 2.2.8. Study Measures and Data Collection Schedule

Assessments will occur at baseline, 12, and 24 months on clinical, behavioral, and psychosocial outcome measures at one of the PAMF clinics from which participants are recruited (**Table 2**). These include the following primary and secondary outcomes and potential effect modifiers and mediators.

### 2.2.8.1. Primary and secondary outcomes (Aim 1)

Primary outcome, weight, will be assessed according to standard protocols. Secondary outcomes include measures of cardiometabolic risk factors (e.g., BMI, waist circumference, and blood pressure), psychosocial well-being (e.g., health-related quality of life), and behavior change (e.g., diet, physical activity). Trained bilingual research assistants will conduct anthropometric and blood pressure measurements, and multiple-pass 24-hour dietary recalls. Online self-administered questionnaires and in-person interviewer-administered questionnaires (see **Table 2**) will be used to assess additional secondary outcomes including physical activity, health-related quality of life, obesity-specific quality of life, depressive symptoms, and sleep habits and quality. All these surveys have been validated in English and Spanish. Additionally, we will abstract data from the EHR on laboratory values (e.g., HbA1c, fasting glucose, lipid levels), medication prescriptions, and health care encounters for 24 months before and after randomization.

### 2.2.8.2. Potential effect modifiers and mediators (Aim 2)

To complement the primary and secondary outcomes, we will explore for whom and under what condition (effect modifiers) and how (effect mediators) treatment effects occur. Potential modifiers include sociodemographics (e.g., age, sex, education, employment, occupation, marital status, household size, income, country of origin), food insecurity, acculturation, and health literacy. Potential mediators include self-efficacy, social support, and intervention adherence. Intervention adherence will be tracked using session attendance, self-monitoring data, and communication between the participant and coach.

### 2.2.8.3. Process evaluation (Aim 2)

To help contextualize the effectiveness evaluation under Aim 1, we will conduct a detailed process evaluation with mixed methods to gain a nuanced understanding of why the intervention is (or is not) superior to usual care, whether high intervention fidelity is achieved, what barriers and enablers there are, how these may translate into future implementation, and what modifications can maximize implementation success. We frame the process evaluation around the RE-AIM framework's reach, adoption, implementation, and maintenance domains (**Table 3**). We will conduct in-depth interviews with patients, recruitment staff, intervention staff, physician champions, and community stakeholders at baseline, study mid-point, and end point according to each RE-AIM component. The interview guides will be adapted from guides that were developed for the same purpose in another ongoing trial.

## 2.2.9. Statistical Analysis

### 2.2.9.1. Analytical plan

The primary hypothesis that intervention participants will achieve and maintain lower weight at 24 months than controls will be tested in a repeated-measures mixed model (Aim 1). Secondary hypotheses are analogous, but with different outcome variables, and will be tested using repeated-measures, mixed-effects, linear (for continuous variables) or logistic models (for discrete variables).

$$Y_t = \beta_0 + \beta_1 X + \beta_2 Y_0 + \beta_3 T + \beta_4 (XT) + \sum \beta_{4+i} Z_i + \alpha + \gamma + \varepsilon \quad (1)$$

Let  $Y_t$  be participants' post-randomization values of the outcome variable at visit T (12 or 24 months). Given the covariate-adaptive randomization, distributions of baseline values on the outcome variable ( $Y_0$ ) and randomization balancing factors ( $Z_i$ ) (clinic, age, sex, BMI, waist circumference, and level of acculturation) should be similar between study arms (X) and thus not bias the results. But to the extent they are associated with the outcome, their inclusion in the model will account for otherwise unexplained variation and hence increase efficiency;  $\alpha$  and  $\gamma$  are random effects due to clustering of patients within physicians and, in turn, physician within clinics, and patients with intervention classes. The random error,  $\varepsilon$ , accounts for the non-independence of repeated measures using a covariance structure within participants to be determined by the least Bayesian information criterion. The primary analysis will follow ITT principles and use all available follow-up data, with missing data handled directly through maximum likelihood estimation in mixed modeling. We will document the extent and pattern of missing data and the reasons, and will conduct sensitivity analyses of the impact of missing data on stability of the primary results. For example, we may use available weights up to the point after which data are no longer available (e.g., dropouts) or should not be used (e.g., pregnancy) and then employ multiple imputation based on a predictive distribution for future weights with the mean possibly adjusted depending on the pattern and extent of missing data. We will verify that mixed model-based results are not sensitive to violations of model assumptions with permutation and bootstrap resampling tests.

Subgroup analyses of pre-specified potential modifiers (**Table 2**) of the intervention effect on weight change will be performed by expanding equation 1 to include the appropriate modifier-by-study-arm interactions. Testing whether the  $\beta$  coefficients of the interaction terms are equal to zero is equivalent to testing the null hypothesis that the subgroup of interest does not independently modify the intervention effect.

Longitudinal (e.g., change in mediator from baseline to 12 months and change in primary outcome from 12 to 24 months) and contemporaneous (e.g., changes in mediator and outcome from baseline to 24 months) mediation will be examined separately by MacKinnon's product of coefficients test ( $\alpha\beta$ ). Asymmetric confidence limits will be constructed based on the distribution of the product with the PRODCLIN program. Because multi-collinearity may be present in multiple mediator models, we first will test each mediator in single-mediator models. Multiple-mediator models including all variables that are at least marginally significant in the single-mediator models will test for independent and suppression effects. To determine the extent of mediated effect, the percentage of total effect mediated will be calculated for each significant mediator as  $\alpha\beta/(\alpha\beta + \gamma)$ , where  $\gamma$  is the direct intervention effect on outcome. The effect modification-mediation analyses are hypothesis generating only, but we pre-specify the variables to ensure a focus.

We will analyze the quantitative process data using standard tests (e.g., Student's  $t$ -tests for continuous variables and  $\chi^2$  tests for categorical variables). These analyses will be descriptive and not inferential. We will transcribe, code, and analyze qualitative data using Atlas.ti. We will develop a codebook of codes and definitions based on the RE-AIM domains assessed, and use it to train coders and guide data coding. To identify themes we will use content analysis methods. We will triangulate data from different sources to increase the validity of the qualitative data and to draw conclusions about reach, adoption, implementation, and maintenance of the intervention that would guide future implementations.

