### 2.2.3. Randomization and Blinding

Eligible participants will be randomized in a 1:1 ratio to receive usual care or usual care plus the intervention ( $n = 93/\text{arm}$ ). We will apply a covariate-adaptive biased coin method that we have published and used successfully in several trials to achieve good marginal balance between treatments across the following baseline characteristics: clinic, age, sex, BMI, waist circumference, and level of acculturation assessed by the Short Acculturation Scale for Hispanics. The dynamic block randomization algorithm of our method automatically ensures allocation concealment. By design, treatment will be identifiable to participants and the lifestyle coach, but masking of the investigators, Data and Safety Monitoring Board, outcome assessors, and data analyst will be enforced. The bilingual and bicultural lifestyle coach will be masked to participants' official study measurements, but not their self-measurements tracked on MyFitnessPal.

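### Equation 1 leaves the intervention-class effect undefined for controls, and the plan pairs a handful of classes with maximum likelihood and no small-sample method

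*Protocol*

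**What the plan says.** Protocol 2.2.9.1 prints the primary model. Equation 1 has fixed effects for arm, baseline value, visit, arm by visit and the balancing factors (clinic among them), then two random terms, alpha and gamma, and a residual. The random terms are described as "random effects due to clustering of patients within physicians and, in turn, physician within clinics, and patients with intervention classes". Neither is multiplied by the arm indicator.

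The same section says that missing data are dealt with through maximum likelihood. It names no other estimation method and no degrees-of-freedom method. Model assumptions are to be checked "with permutation and bootstrap resampling tests"; the resampling unit is not given.

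Section 2.2.2 has three sequential cohorts of 62, each from its own clinic, and only patients assigned to the intervention go to the group sessions. Section 2.2.3 states: "Eligible participants will be randomized in a 1:1 ratio to receive usual care or usual care plus the intervention". The number of classes per cohort is not given.

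**The concern.** Patients who share a class share a coach, a room and a group dynamic, so their 24-month weights may be correlated. Controls have no such grouping. A model for this partially nested design must say that the class effect exists in one arm only. Equation 1 does not, so for half the sample one term of the primary model has no stated value.

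The second difficulty is the number of classes. A between-class variance estimated from three, six or nine groups by maximum likelihood is biased towards zero, and a normal reference ignores the uncertainty in it. The standard error for the arm effect is then too small, and the primary test rejects too often under the null.

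Third, clinic is entered twice. As a balancing factor it is a fixed effect, and in the description of the random effects it is the level above physician. Three clinics are too few to estimate a clinic variance.

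**Working it through.** **1. The plan's own figure.** Section 2.2.9.2 states: "A sample of 93/arm has 80% power to detect a net between-treatment" and "difference of 2.1(4.6) kg, assuming up to a 20% loss to 24 months of follow-up". It uses a t-test "with simplified assumptions that compares (24m - baseline) differences between study arms", with no clustering term.
- Evaluable per arm: 93 × 0.80 = 74.4.
- SE = 4.6 × √(2/74.4) = 0.754 kg; 2.1/0.754 = 2.78.
- Power ≈ Φ(2.78 − 1.96) = 0.795 (0.790 with the t distribution). The stated 80% reproduces.

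**2. Inputs not in the document (assumptions).** Class ICC 0.02 to 0.05; one, two or three classes per clinic. Enrolled intervention patients per cohort: 62/2 = 31. Evaluable: 74.4/3 = 24.8, so class size m is 24.8, 12.4 or 8.27.

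**3. What class clustering does if it is not captured.** Design effect in the intervention arm only: DE = 1 + (m − 1) × ICC. Ratio of true to naive SE: √((1 + DE)/2). Type I error if the clustering is missed: 2 × (1 − Φ(1.96/ratio)).

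| Classes per clinic | ICC | DE | SE ratio | Type I if missed |
|---|---|---|---|---|
| 1 | 0.02 | 1.476 | 1.113 | 7.8% |
| 1 | 0.05 | 2.190 | 1.263 | 12.1% |
| 2 | 0.02 | 1.228 | 1.055 | 6.3% |
| 2 | 0.05 | 1.570 | 1.134 | 8.4% |
| 3 | 0.02 | 1.145 | 1.036 | 5.8% |
| 3 | 0.05 | 1.363 | 1.087 | 7.1% |

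**4. Does maximum likelihood capture it?** Take one class per clinic, 25 patients per arm per clinic, clinic fixed, ICC 0.05. With residual variance σ², the class variance is (0.05/0.95)σ² = 0.0526σ². Let d_k be the arm difference in clinic k and SS the sum of squares of the three d_k about their mean. Then SS is distributed as (0.0526 + 2/25)σ² × χ²(2) = 0.1326σ² × χ²(2).
- ML gives a class variance above zero only if Σ(25(d_k − d̄)/2)² > 3 × 25σ², that is SS > 0.48σ². The probability is exp(−(0.48/0.1326)/2) = 0.16. In about 84% of trials ML sets the class variance to zero.
- Under REML the threshold falls to its null expectation, SS > 2 × 0.08σ² = 0.16σ². The probability is exp(−(0.16/0.1326)/2) = 0.55.

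**5. Simulated type I error at a nominal 5%, class effect in the intervention arm only, ML with normal reference.** Simulation A: 1,500 null trials per setting, 25 per arm per clinic. Simulation B: 2,000 trials, 75 per arm. Both treat clinic as fixed.

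| Classes per clinic | A, ICC 0.02 | A, ICC 0.05 | B, ICC 0.05 |
|---|---|---|---|
| 1 | 8.0% | 11.3% | 11.7% |
| 2 | 6.7% | 6.1% | 7.5% |
| 3 | 5.5% | 7.2% | 6.3% |

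In B, ML put the class variance at zero in 83%, 59% and 52% of trials, in line with step 4. With one class per clinic the mean SE was 0.795 against a true spread of 0.956. At ICC 0.02, B gave 5.4% with two classes and 5.8% with three. A further simulation of the same design, over ICC 0.02 to 0.05, gave about 9 to 11% with one class and 6.6 to 7.7% with two or three. Simulation error near 5% is about 0.5 points.

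**6. How much is due to the coding of controls?** Simulation B at ICC 0.05, ML, for one / two / three classes per clinic:
- controls without a class effect: 11.7 / 7.5 / 6.3%
- each control a class of one: 10.2 / 7.2 / 7.0%
- each cohort's controls as one class: 12.5 / 8.2 / 5.5%
- all controls as one class: 11.7 / 7.9 / 7.0%
- class term left out: 14.1 / 8.6 / 8.0%

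With one class per clinic the mean SE ranges only from 0.76 to 0.82 across the codings that keep the term.

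**7. What the remedy does.** REML with controls given no class effect: 8.0 / 5.5 / 5.1% at ICC 0.05 with a normal reference. Adding class-based degrees of freedom gave about 4 to 5% in one simulation. In another, a class-level Satterthwaite test gave 6.5 to 7.2% with one class per clinic, about 6% with two and about 5% with three.

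**The case against.** The best defence is that equation 1 is schematic. It carries no participant, physician or class subscripts, the text ties the term to intervention classes, and the coding of controls can sit in an analysis plan that is not shown. The maximum likelihood phrase concerns missing data and need not exclude REML. All of that is fair, and it rules out the claim that the protocol gives controls a class effect; it does not say so. What remains is that the protocol itself prints the primary model, without the arm restriction, and names one estimation method and no small-sample correction.

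Several stronger readings are tempting, and the documents do not support them.
- *The result turns on how controls are coded.* Step 6 shows otherwise: the inflation is similar under every coding.
- *Power collapses.* That requires coding each clinic's controls as a class and testing arm on 2 degrees of freedom. The plan states no such test, and with no class correlation the same standard error with a normal reference gives about 80%.
- *Choosing the covariance "using a covariance structure within participants to be determined by the least Bayesian information criterion" undermines the standard error.* The rule is objective and fixed in advance. With two follow-up visits and an assumed correlation of 0.7, simulated type I error after selection was 4.4 to 5.5% for 12-month SDs of 3.6 to 4.6 kg against 4.6 at 24 months. A smaller simulation (700 trials, SDs 4.2 and 4.9) gave 6.6% against 5.6% for unstructured. Neither amounts to a fault.
- *The permutation and bootstrap checks ignore the classes and the "covariate-adaptive biased coin method".* The plan does not state the resampling unit, which is a different matter. The balancing factors are in the model, and the permutation reference concerns covariate-adjusted tests.

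On clinic, physicians nested within a fixed clinic effect is a coherent reading, and a redundant random clinic term would largely be absorbed. The wording is ambiguous, with no size attached.

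**Conclusion.** The point holds in a limited form. The class term of the primary model is undefined for controls. With few classes, maximum likelihood and a normal reference, the primary test would be too liberal: roughly 8 to 12% with one class per clinic and about 5.5 to 8% with two or three, at ICCs of 0.02 to 0.05. An arm indicator alone does not cure this; the estimation method and degrees of freedom matter more.

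The ICC range, the class counts and the normal reference are assumptions. With an ICC of zero there is no inflation (4.2 to 5.1% with two or three classes per clinic in simulation B). The simulations use one outcome per patient and leave out physician clustering. To call the primary interval untrustworthy would go beyond this evidence.

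**What to change.** Before the data are unblinded, amend 2.2.9.1 as follows.
- Multiply the class effect by the arm indicator and state that controls have none. State the number of classes per cohort.
- Keep clinic as a fixed effect only, with physicians as a random effect nested within it.
- Fit by REML, and test the 24-month arm contrast with Kenward-Roger or Satterthwaite degrees of freedom. REML uses all available follow-up data in the same way, so the handling of missing data is unchanged.
- Name the resampling unit and keep whole classes together in the bootstrap.

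The cost is a paragraph of text and a few lines of code; trial conduct is not affected. The downside is slightly wider confidence intervals. With a single class per clinic the correction may still leave the test a little liberal (up to 6.5 to 7.2% in one simulation), and the report should then say so.
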